## Methods: participants, interventions, and outcomes

### Study setting {9}

Participants will be recruited from a population referred to tertiary pain clinics at three sites in Sweden: (1) Pain Rehabilitation Clinic of Skane University Hospital in Lund, (2) Pain Centre Sahlgrenska University Hospital in Gothenburg, and (3) Pain and Rehabilitation Centre in Linköping.

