### Eligibility criteria {10}

Inclusion criteria are age ≥ 18 years with long-term (> 3 months) non-malignant pain and long-term prescribed opioid consumption (> 3 months) with a participant and/or prescribing doctor calling for tapering of opioids. All pain classes will be included, i.e., nociceptive pain (both somatic (musculoskeletal) and visceral), neuropathic pain, and nociplastic pain. Tapering of opioids is thus proposed without regard to pain mechanism or diagnoses. The requirement regarding functioning is (1) that a participant is able to absorb and retain information and is thus able to make an informed decision and (2) is at a functional level that permits outpatient visits.

Exclusion criteria at baseline are repeated intake of non-prescribed opioids or other illegal drugs, refusal to perform drug screening, prescription periods shorter than 3 months, and perceived medical risks of waiting with tapering of opioids (e.g., raising opioid doses after acute pancreatitis caused by excessive alcohol intake or kidney disease stage 4–5 in combination with excessive alcohol intake and high doses of opioids). The occurrence of substance use disorder without the use of illicit drugs is not an exclusion criterion.

Exclusion criteria were selected as a safety option to the physician at baseline visit when estimating the individual risks of the ongoing opioid treatment with regard to both overdose and development of dependence whenever a short duration (< 3 months) of treatment has occurred.

Otherwise, eligible participants who chose to not be included in the Swedish Quality Registry for Pain Rehabilitation (SQRP) will also be excluded.

The intervention will be carried out by physicians and nurses employed at tertiary pain clinics.

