## Assignment of interventions: allocation

### Sequence generation {16a}

The allocation sequence is generated by computer to intervention or control in ratio 1:1 and is thereafter kept in sealed envelopes prepared by independent staff for an allocated group of 140 participants. Sealed envelopes will be kept in Lund and allocation will consequently take place in Lund.

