### Implementation {16c}

The sealed envelopes are stored in a locked storage and will be assigned and opened by a physician at baseline visit upon a decision of the participant to participate in a structured tapering process.

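### For a three-site trial the article does not say how an envelope held in Lund is opened at a baseline visit elsewhere, and it lets the physician who judges the risk of waiting also open it

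*Protocol article*

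**What the plan says.** All of this is in the protocol article.

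- **Sequence generation {16a}.** The sequence is computer-generated in a 1:1 ratio and is then "kept in sealed envelopes prepared by independent staff for an allocated group of 140 participants". On custody and place: "Sealed envelopes will be kept in Lund and allocation will consequently take place in Lund".
- **Implementation {16c}.** "The sealed envelopes are stored in a locked storage", and they "will be assigned and opened by a physician at baseline visit upon a decision of the participant to participate in a structured tapering process".
- **Concealment mechanism {16b}.** The text under this heading deals only with the absence of blinding. It describes no concealment procedure.
- **Study setting {9}.** "Participants will be recruited from a population referred to tertiary pain clinics at three sites in Sweden". These are Lund, Gothenburg and Linköping. The version log says the two added centres will both recruit and deliver the intervention.
- **Eligibility criteria {10}.** One exclusion is "perceived medical risks of waiting with tapering of opioids". On who applies the criteria: "Exclusion criteria were selected as a safety option to the physician at baseline visit".
- **Consent {26a}.** Physicians obtain consent at the baseline visit.
- **Order of steps.** A heading under Interventions places information and screening before randomisation. Intervention description {11a} places the written treatment plan after randomisation, at the same visit.

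**The concern.** Two things do not fit.

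1. **Place.** {16a} keeps envelopes and allocation in Lund, while {16c} has the envelope opened at the baseline visit. In Lund these agree. For a visit in Gothenburg or Linköping a linking step is needed, and none is given.
2. **Role.** The physician at the baseline visit takes consent and applies the exclusions, and a physician at that visit opens the envelope. One exclusion is a judgement about the danger of waiting. It has a consequence only if the envelope assigns the delayed arm, because a participant who starts at once does not wait. {16c} ties opening to the participant's decision, not to a completed and recorded eligibility judgement.

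At stake is selective removal of patients from one arm. If a physician sees a waiting-list allocation and only then concludes that this patient should not wait, the control arm loses its higher-risk patients and the intervention arm does not. The trial is fully open ({17a}), so no later blinding limits the effect.

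**Working it through.** **Step 1: the sections side by side.**

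| Question | Answer in the article | Section |
|---|---|---|
| Where are envelopes kept, and where does allocation happen? | Lund | {16a} |
| Who opens, and when? | A physician, at the baseline visit | {16c} |
| Where are baseline visits held? | Three recruiting sites; not tied to Lund | {9}, version log |
| Who takes consent? | Physicians at the baseline visit | {26a} |
| Who judges the exclusions? | The physician at the baseline visit | {10} |
| Must eligibility be recorded before opening? | Screening is placed before randomisation; no recording step is stated | Interventions, {16c} |
| Is the opener someone other than the enroller? | Not stated | {16b}, {16c} |

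The linking step for the two other sites and the separation of roles are the blanks.

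**Step 2: allocations still open.** Trial status reports 62 allocated out of 140. 140 − 62 = 78 remained when the article was written.

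**Step 3: the plan's own figure.** Sample size {14} gives 70 per group from d = 0.5, 80% power, α = 0.05 and 10% drop-off. With a two-sided normal approximation this is 63 per arm, and 63 / (1 − 0.10) = 70. The figure reproduces. It neither supports nor weakens the point and serves only as the arm size below.

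**Step 4: an illustration on assumed inputs.** The documents give no rate of exclusion after opening and no dose distribution. Suppose k of 70 control patients are removed after opening, each with r times the arm's mean baseline dose. The remaining mean, relative to the full arm, is

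(1 − (k/70)·r) / (1 − k/70), which is a fall of k(r − 1) / (70 − k).

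| k removed | r = 1.5 | r = 2 |
|---|---|---|
| 2 | 1.0/68 = 1.5% | 2/68 = 2.9% |
| 5 | 2.5/65 = 3.8% | 5/65 = 7.7% |
| 10 | 5/60 = 8.3% | 10/60 = 16.7% |

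If the SD equals the mean (also assumed), these are shifts of 0.015 to 0.17 SD. The case k = 5, r = 2 gives about 0.08 SD, or 0.077/0.5 ≈ 15% of the design effect. If doses under usual care stay near baseline, the shift lowers the control mean at 4 months and so shrinks the apparent dose benefit.

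**Step 5: would the analysis repair it?** In this scenario the k patients had already been allocated. Keeping all 70 in the comparison restores the mean exactly. Retention {18b} already plans to retrieve register doses for participants who discontinue or deviate. However, Statistical methods {20a} compares groups per protocol, among those who attend the 4-month follow-up or the second baseline visit. A patient judged unable to wait after opening would probably not be in that set, and might not be counted as a participant at all.

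**The case against.** The best defence is that the stated order is sound: screening, then the participant's decision, then the envelope, then the treatment plan. The dose calculation, benzodiazepine check, interview, drug screen and alcohol marker all fall under the heading that precedes randomisation, and these inform the risk judgement. {16c} says a physician, not the enrolling physician. The reference to the baseline visit can mean when and not where. A Lund physician opening envelopes on request while the visit takes place elsewhere would satisfy both sections. Computer generation, sealing, independent preparation and locked storage are genuine safeguards. A record-and-lock step is also the kind of detail a condensed article may leave to the full protocol.

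Most of this stands, and it rules out three stronger readings that a reader might infer.

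- **That {16a} and {16c} cannot both be true.** They can, if allocation is released from Lund on request. The article does not say that this is done.
- **That concealment failed, or that enrollers could foresee allocations.** No section gives a physician knowledge of an allocation before opening, or custody of the envelopes outside locked storage.
- **That the bias would be beyond repair.** The harm described is exclusion after allocation, which analysing everyone allocated would largely undo.

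The defence does not supply the missing link for Gothenburg and Linköping, and it does not bar the enrolling physician from opening the envelope. Nor does it explain why the section headed as the concealment mechanism contains none.

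**Conclusion.** The point holds as a gap in how allocation is fixed. The allocation sections do not join up for a three-site trial, and they allow one physician to take consent, judge an exclusion that matters in only one arm, and open the envelope. Screening before randomisation and the envelope safeguards reduce the risk. They do not close it, because opening is not tied to recorded eligibility.

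Nothing shows that selective exclusion has occurred, and its size cannot be derived from the documents. The 1.5% to 16.7% range rests wholly on assumed numbers removed and assumed dose ratios. The SD figures also assume an SD equal to the mean. That one person holds all three roles is an inference from {10}, {26a} and {16c} read together. Absent details such as envelope opacity, numbering or block size are not counted, since the full protocol may hold them.

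This is a worthwhile, inexpensive improvement while allocations remain open. It is not a defect that invalidates the trial.

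**What to change.** Reconcile {16a}, {16b} and {16c} so that they describe one procedure for all three sites:

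1. The enrolling physician irrevocably records consent and the baseline-visit eligibility judgement, including the one on risk of waiting.
2. Only then is the allocation released, either by phone from a person in Lund not involved in enrolment or from the REDCap system the trial already uses (Data management {19}).
3. {16b} states this as the concealment mechanism and leaves blinding to {17a}.
4. Every participant whose allocation was released stays in the randomised set for the MME comparison, in the arm assigned, using the register data foreseen in {18b}. This should expressly cover anyone judged ineligible after release. The per-protocol comparison in {20a} can be kept alongside.

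The change applies to the 78 or so allocations remaining at the time of the article and alters no clinical criterion. It costs some protocol wording, a small set-up and a short delay at the visit. For the allocations already made, the trial team could report how many envelopes were opened and how many of those patients were later excluded, by arm. That would show whether the risk materialised.

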### Concealment mechanism {16b}

Blinding of participants or health care professionals is not possible due to the nature of the intervention, and no blinding will be performed in the assessment of outcomes or data analysis.

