#### Primary outcomes

Consumption of opioids, measured as MME, will be evaluated using data extracted from the Swedish drug register of the National Board of Health and Welfare (SDPR) where registration of all withdrawals of prescribed drugs is made. MME will be calculated using these data. At all baseline visits and 12-month follow-ups, the MME will be calculated for the preceding 90 days, but at 4 months after the intervention, the dose will be calculated for the preceding 30 days as the intervention is estimated to last approximately 3 months.

Self-reported opioid consumption will also be evaluated and reported in MME. Calculation of morphine equivalent dose will be performed with conversion factors used in Cochrane review [7].

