## Assignment of interventions: blinding

### Who will be blinded {17a}

No blinding at any time will be performed.

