### Confidentiality {27}

Data confidentiality will be protected in accordance with the routines of SDPR and SQRP. Additional data kept in REDCap® will be coded with study ID at each study center, and no other data providing personal identification will be kept. Linking of databases will be performed by the National Board of Health and Welfare.

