## Statistical methods

### Statistical methods for primary and secondary outcomes {20a}

All statistical analyses will be performed with the SPSS software (version 25, IBM Inc). Continuous data will be expressed by means, standard deviation and 95% confidence interval, and categorical data in numbers and percentages.

The intervention arm (tapering opioids) will be compared with control (waiting list) for primary and secondary outcomes at 4 months of follow-up. Statistical analysis of differences between groups will be performed per protocol (attending follow-up 4 months after the start of the intervention and attending second baseline visit in controls) with a paired *t*-test regarding the primary outcome and a Wilcoxon signed-rank test regarding secondary outcomes.

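### The protocol rules out blinding of outcome derivation and analysis for a reason that covers only participants and staff; register-based dose could be derived and compared with the arm code withheld, once the dose windows are the same in both arms

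*Protocol article*

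**What the plan says.** Two sections of the protocol article settle blinding. Under Concealment mechanism {16b} it says that "no blinding will be performed in the assessment of outcomes or data analysis". Under Who will be blinded {17a} it adds: "No blinding at any time will be performed". The reason, also in {16b}, is that "Blinding of participants or health care professionals is not possible due to the nature of the intervention".

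The Primary outcomes section names the source: "Consumption of opioids, measured as MME, will be evaluated using data extracted from the Swedish drug register of the National Board of Health and Welfare". The same section adds: "Self-reported opioid consumption will also be evaluated and reported in MME". The register data are collected once, after all follow-ups have closed (Plans for assessment and collection of outcomes {18a}). On linkage, Confidentiality {27} says: "Linking of databases will be performed by the National Board of Health and Welfare". Allocation is recorded in REDCap with the additional data (Data management {19}).

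The between-group comparison is at 4 months and per protocol, defined as "attending follow-up 4 months after the start of the intervention and attending second baseline visit in controls" (Statistical methods {20a}). Participants who still do not follow a renewed treatment plan are left out of the final analysis (Criteria for discontinuing or modifying allocated interventions {11b}). The Data Availability statement keeps data collection, analysis and interpretation within the group of researchers.

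**The concern.** The stated reason and the stated decision do not match. Treated patients and treating staff cannot be blinded to a tapering programme. That does not explain why the arm must be known when register rows are converted to dose, when the analysis set is fixed, or when the test is run.

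At stake is protection against choices made with the arm in view. A register of dispensings is not a daily dose: someone has to handle packs that straddle a window, overlapping packs and as-needed prescriptions. Someone also has to settle who counts as per protocol and who is excluded. The research group hypothesises superiority and, by the Data Availability statement, does this work itself. There is no data monitoring committee ({21a}) and no auditing ({23}), so masked derivation would be one of few available safeguards.

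**Working it through.** **Design figure.** The only design figure is 70 per group (Sample size {14}: effect size 0.5, 80% power, alpha 0.05, 10% drop-off). Two-sided, n = 2 × (1.960 + 0.842)² / 0.5² = 62.8, so 63 per group; 63 / (1 − 0.10) = 70. It reproduces. Masking the arm enters none of these inputs, so sample size, alpha and power stay as they are.

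**Does the reason cover the step?**

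| Step | Reason in {16b} applies? | Can the arm be withheld? |
|---|---|---|
| Participant, treating staff | Yes | No |
| Self-reported dose, at source | Yes, given by unblinded participants | No |
| Register extract converted to dose | Not addressed | Yes, in part |
| Fixing the analysis set | Not addressed | In part; it can be locked before results by arm are seen |
| Running the 4-month comparison | Not addressed | Yes, by coded labels |

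**Is withholding feasible?** The register data arrive in one extraction after follow-up closes, the linkage is done by an outside agency, and allocation sits in REDCap. Withholding the arm field therefore touches no patient contact. When the article was written, 62 of 140 participants had been allocated (Trial status) and no register data had been collected under the plan.

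**The obstacle in the document itself.** Primary outcomes sets a 90-day window at every baseline visit. For the later assessment it reads: "at 4 months after the intervention, the dose will be calculated for the preceding 30 days as the intervention is estimated to last approximately 3" (the unit is months). The controls' assessment for the 4-month comparison is their second baseline visit ({20a}). Taken literally:

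- intervention arm at 4 months: 30-day window;
- control arm at 4 months: 90-day window.

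Whoever derives the dose would need the arm to choose the window, or could read the arm from it. The windows have to be aligned before masked derivation can work.

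**How much can hang on a derivation rule?** This is an illustration under an assumed rule that counts a pack wholly on its dispensing date, for a person on daily dose D who collects a 30-day pack (Intervention description {11a} gives prescribing intervals of 7 to 30 days):

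- 30-day window: pack just inside gives 30D / 30 = D; just outside gives 0.
- 90-day window: one pack contributes 30D / 90 = D/3.

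This shows how sensitive an individual's value is to such rules. It does not measure bias from unblinding, since a rule fixed in advance would leave no room for judgement.

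**The case against.** The strongest case against has four parts.

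1. *Masking would hide little.* Tapering steps of about 5–10% of the starting dose each week, a switch to one extended-release product, short prescribing intervals and possible multi-dose dispensing all show in register rows. Controls also have an 8-month assessment and 16 months of enrolment against 12, so a full set of index dates would reveal the arm. This stands as a limit. Cutting the working extract at 4 months from randomisation removes the later dates, but the dispensing pattern remains.
2. *Derivation rules belong in an analysis plan that is not shown.* Correct: the absence of pack-handling rules is not a finding here, and well-specified rules would remove much of the discretion. But the lack of blinding is stated outright in the protocol, and an analysis plan that masked the analyst would contradict it.
3. *Part of the primary outcome cannot be masked.* Self-reported dose comes from unblinded participants. True at source; its comparison can still be run under coded labels.
4. *The open-label design is disclosed and consistent.* True, but disclosure does not supply a reason for the two steps that the stated reason leaves out.

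A reader might infer three stronger things. One is that masking costs nothing; the unequal windows show that something must change first. Another is that treating clinicians derive the dose knowing the arm; the document says only that the work stays within the research group. The third is that the outside agency derives the dose; it is assigned the linkage and nothing more.

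**Conclusion.** The point holds in a limited form. Blinding of outcome derivation and analysis is ruled out without a reason that applies to those steps, although the register-based part of the primary outcome could be handled with the arm withheld. The gain is a partial reduction in the risk of bias in an open-label, per-protocol analysis done by the trial's own group. It is worth making, but the trial does not fail without it.

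The document gives no basis for a size of bias, and it would be wrong to infer that the results will be biased. The conclusion rests on two assumptions: that the research group itself derives dose and decides analysis-set membership, as the Data Availability statement implies; and that someone in the group can work without access to the allocation field.

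**What to change.** Amend {16b} and {17a} to state that participants and staff are unblinded, and that:

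- register dose at 4 months from randomisation is derived with allocation withheld, using the same window or windows in both arms. Deriving both the 30-day and the 90-day value for everyone would do, with the one used for the comparison named in advance;
- the derived dose and analysis-set membership, including exclusions under {11b}, are locked before the code is released;
- the 4-month comparison, including self-reported dose, is first run with the arms coded A/B.

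Primary outcomes and {20a} need matching wording so that the window no longer depends on the arm.

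Cost: amended text in those sections, a formal amendment under {25}, and one variable held back until lock. No extra patient contact or data collection is needed. What remains is that masking will be incomplete, because of dispensing patterns and unblinded self-report.

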### Implementation {16c}

The sealed envelopes are stored in a locked storage and will be assigned and opened by a physician at baseline visit upon a decision of the participant to participate in a structured tapering process.

## Assignment of interventions: blinding

### Who will be blinded {17a}

No blinding at any time will be performed.

### Procedure for unblinding if needed {17b}

Not applicable.

## Data collection and management

### Plans for assessment and collection of outcomes {18a}

#### Primary outcomes

Individual data from the SDPR will be collected when all follow-ups are closed [51]. Self-report of daily opioid consumption at the time of the visit will also be assessed.

#### Secondary outcomes

Before a baseline visit, a phone call by a study nurse to orally inform about the trial is made and a questionnaire with secondary outcomes and baseline characteristics is mailed to participants as a part of reporting to SQRP, but with a reduced content for the study population [32]. Participants denying tapering are reported to SQRP only at baseline visits. A fulfilled questionnaire is required to be scheduled at a baseline visit for all participants. The baseline visit must occur within 3 months after the questionnaire has been filled out.

The follow-up questionnaire is sent by mail 1 month before time points: 1 month (all participants), 8 months (controls), and 12 months (all) after the start of tapering.

Twelve months after the start of tapering, a phone call by administration staff is followed by a mailed questionnaire.

